The Safe Steps model has generated interest in mental health services across NSW, with training on the model recognised and recommended for implementation in other services. It has been further developed into a full programme that includes meaningful cultural consultation, peer and advocate involvement, and multi-professional input, as part of a multi-site translational research. Informing its further development is a range of knowledge bases on the value of therapeutic relationships, recovery, lived experience involvement, choice [36,37], trauma-informed care [38], mental health nursing emotional capabilities [38,39], mental health nurses’ professional identities [40,41], mental health nursing specialist education and training [42–44], and restorative approaches [45,46].

This protocol outlines a proposed series of studies evaluating the Safe Steps for De-escalation model, which was developed to address several gaps in the academic mental health literature. The model offers a structured approach to therapeutic responding, grounded in content, input, and participation from diverse key stakeholders, from intervention design, implementation, through to evaluation. The proposed evaluation addresses three core objectives and tests two overarching hypotheses. The first objective is to examine the effectiveness of the Safe Steps in reducing restrictive practice events, duration, and physical injuries. It was hypothesised that intervention units would show more significant reductions in IRR of restrictive practice events (defined as seclusion, physical restraint, and sedation via intramuscular injection [IMI]), estimates of restrictive practice duration (i.e., seclusion and physical restraint duration), and IRR of physical injuries, compared to control groups and within-group baseline. The second objective is to assess whether the Safe Steps improves people’s experience of services and perceived staff action on violence prevention, and nurses’ professional quality of life and demonstrated emotionally intelligent workplace behaviours. It was hypothesised that scores from these four measures at the final time point would be significantly higher than at baseline. Lastly, the third objective is to explore factors influencing the successful, pragmatic implementation of the Safe Steps.

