**Fig 1 pone.0325558.g001:**
[figure not shown]
Concurrent mixed methods design diagram.

The effectiveness of the Safe Steps will be evaluated in three adult mental health inpatient units, as using multiple sites and varying the setting and context reduces the risk that findings are limited to the experimental setting [49]. Between March 2023 and April 2025, baseline and one-year follow-up outcomes will be assessed (see Fig 2), as implementation efforts on reducing restrictive practices are said to be consolidated within 12 months [50]. Four quarterly time points will be applied to align with the phased deployment of the Safe Steps’ training component, which would allow for the assessment of short-, medium-, and long-term outcomes and prevent misjudging the intervention’s effectiveness based on insufficient timeframes [51].

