**Fig 2 pone.0325558.g002:**
[figure not shown]
Outcomes and data gathering timeline. CEO-MHS = Consumer Evaluation of Mental Health Services; EI = emotional intelligence; eMeds = electronic medication management system; IMI = intramuscular injection; ims+ = incident management system; ProQOL = Professional Quality of Life; VPC-M-FR = Modified Violence Prevention Climate.

There will be three forms of comparisons within the current evaluation. Between- i) and within-group ii) comparisons will be applied to test the first and second sets of hypotheses. The third will be a between-cluster comparison iii), intended to identify the most active co-occurring therapeutic and nursing responses (clusters) contributing to the Safe Steps’ overall impact. The first set of hypotheses is that implementation units will exhibit greater reductions in the IRR for restrictive practice events, the estimate of restrictive practice duration, and the IRR for physical injuries, compared to control groups and their baseline levels. The second set of hypotheses is that measures of service experience, perceived staff action towards violence prevention, nurses’ professional quality of life, and nurses’ perceived demonstration of emotionally intelligent workplace behaviours at the final time point would be significantly higher than at baseline. The between-group comparisons will be conducted exclusively to address the first objective, as these analyses will depend on accessible routine reports on restrictive practices and physical injuries selected for this purpose. Australian public acute mental health services are legally mandated to report on seclusion and physical restraint events and duration as key performance indicators [52]. Events of physical injuries and sedation via IMI are also routinely documented in established information management systems. These routine measures will help minimise performance and detection bias associated with the lack of blinding. Conversely, conducting a between-group comparison on non-routine measures could be cost-prohibitive and challenging to implement, as exemplified by unmet sample size requirements in previous studies [27]. This evaluation will have no randomisation, although covariate balancing will be applied to between- and within-group comparisons in testing the first set of hypotheses.

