### Analysis plan

Quantitative and qualitative analyses will be used to answer the evaluation’s objectives. Consultations with statisticians occurred for the range of statistical treatments employed in this evaluation. Various packages in R [74] and RStudio [60] will be maximised for the quantitative analyses, and Matplotlib [75] will be utilised for visualising outcomes. Each hypothesis will be supported if outcomes are statistically significant at p < .05.

Poisson mixed-effects models [56] will be used for count data and linear regression models for continuous outcomes, to determine whether these outcomes differ according to intervention implementation and time points. Data cleaning and validation, assumption checks, model diagnostics, and follow-up analyses will be undertaken. Negative binomial mixed models, zero-inflated models, and linear mixed-effect models may be used depending on the model’s diagnostics. Covariates in the mixed-effect models will include the acute care unit, calendar month, day, year, and the day within the study period for each daily event aggregate. Model selection will prioritise parsimony and explanatory strength. Inverse probability weighting (IPW) will be applied in the between- and within-group comparisons. Using the ipw package [76], IPW will be used to balance covariates, including but not limited to the average harm scores of daily aggregates, the number of high observation beds, the number of seclusion rooms, and other confounds (i.e., physical restraint and Code Blacks are closely interrelated, influencing each other’s occurrence or implementation [77]). Listed covariates for balancing will be used, subject to the data’s fit and the statistical model’s ability to achieve convergence in the IPW approach.

Hierarchical clustering analysis [78] will support the emergence of co-occurring mental health nursing response clusters, which will then be the fixed effect in modelling differential associations with restrictive practices, physical injuries, and situational aggression. This cluster and regression analysis constitutes the between-cluster comparison to identify the most active response clusters contributing most to Safe Steps’ overall impact.

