Given the quality checks associated with national key performance indicators for mental health services, there is no expected missing data for the primary outcomes. However, log data may undergo multiple imputations under different missing data mechanisms [79] to minimise bias due to missing data. A day without log data will contribute to the missingness rate. Lastly, fidelity scores will be described statistically and plotted in a graph.

For survey-based measures, a one-way analysis of variance will be used to assess differences over time in people measures. In contrast, a paired t-test will examine changes in nurses’ measures over time. Missing data of not more than 20% will be imputed using multiple imputations [80]. Measures with less than 80% of the total items completed will be excluded. Non-parametric statistical models may be used if distributional assumptions are violated.

For the qualitative strand, pluses and wishes, transcribed interview responses, and focus group discussion data, will be analysed using NVivo 12 Pro software [81] and alternatively through a spreadsheet. An analytical process [82,83] that involves re-reading transcriptions for familiarisation, organising data, coding and condensed coding, and refining thematic results through a team approach, will be systematically led by the first author to integrate multiple perspectives. A codebook will be maintained [84]. Individual participants can review their responses for accuracy before analysis [85].

Machine learning techniques, including but not limited to random forest [86] and Boruta algorithm [87], will be maximised to undertake a feature analysis on the most important drivers of aggression and restrictive practice use. Qualitative log responses on triggers of de-escalation will be coded and considered in feature analyses.

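### People-survey hypothesis is final higher than baseline, but the named test is an omnibus one-way ANOVA over time, which an intermediate wave alone can make significant

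*Protocol article*

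**What the plan says.** The hypothesis is stated twice in the protocol article, as a two-point comparison with a direction. The Introduction (The Safe Steps for De-escalation) says: "It was hypothesised that scores from these four measures at the final time point would be significantly higher than at baseline". The Design section repeats it for all four survey measures, ending: "emotionally intelligent workplace behaviours at the final time point would be significantly higher than at baseline".

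The Analysis plan treats the two respondent groups differently. For people receiving care: "For survey-based measures, a one-way analysis of variance will be used to assess differences over time in people measures". For nurses: "In contrast, a paired t-test will examine changes in nurses’ measures over time". It allows non-parametric models if distributional assumptions fail, without naming a comparison. The decision rule for the whole evaluation is: "Each hypothesis will be supported if outcomes are statistically significant at p < .05".

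On timing, the Design section says: "Four quarterly time points will be applied to align with the phased deployment". Which of these points carry the people survey is in Fig 2, which is not shown. The Sample size section asks for at least 135 responses from people receiving care, including a 30% margin for exclusions, for 95% power. It does not say which test that power refers to.

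**The concern.** A one-way ANOVA over time has the null that all wave means are equal. Rejecting it says that at least one wave differs from another. It does not say that the final wave differs from baseline, which is the hypothesis. With three or more waves, a temporary change in the middle of the year can give p < .05 while the final mean is no better than the first. Under the stated rule that would be read as support.

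Two of the four measures under the second objective are affected. At stake is a claim that service experience and perceived staff action on violence prevention improved over the intervention year, resting on a test that does not examine that claim. The usual rank-based replacement for a one-way ANOVA is also omnibus and would carry the same mismatch.

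**Working it through.** **The plan's own figure.** The 135 responses cannot be reproduced, because the article gives no effect size, test or number of groups. Several settings come within 3%: three groups with f = 0.40 (102 × 1.3 = 133), a one-sided two-sample t-test with d = 0.65 (104 × 1.3 = 136), or three groups with f = 0.35 and no margin (132). Four groups with f = 0.40 need 112, or 146 with the margin. These fits all assume an effect size, so they do not settle how many waves were planned.

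**Inputs.** From the article: 135 responses, 30% margin, 5% level, four quarterly time points. Assumptions: equal, independent groups per wave; SD 1; k = 4 waves, with 3 and 5 as a range; effects of 0.5 and 0.8 SD. Removing the margin gives 135 / 1.3 = 104 analysable, or n = 26 per wave. About 34 per wave applies if nothing is excluded (135 / 4).

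**Formulas.** For wave means μ1…μk:
- Omnibus F: noncentrality λ = n Σ(μj − mean μ)², with k − 1 and k(n − 1) degrees of freedom. For k = 4 and n = 26 these are 3 and 100, and the critical F is 2.70.
- Final-minus-baseline contrast with pooled error: noncentrality δ = (μk − μ1) / √(2/n), with 100 degrees of freedom and two-sided 5% critical t = 1.98. Only the upper tail counts as a gain.

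**No baseline-to-final gain (k = 4).**
- Means 0, 0.5, 0.5, 0: λ = 26 × 0.25 = 6.5. F is significant in 54% of trials (67% with 34 per wave). The contrast has δ = 0 and declares a gain in 2.5%.
- Means 0, 0.5, 0, 0: λ = 26 × 0.1875 = 4.875. F is significant in 42% (53%). Contrast 2.5%.
- One intermediate wave raised by 0.5 SD, 104 in total: F is significant in 55% with k = 3 and 32% with k = 5.

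Adding an informal look at the sign does not repair this. The pattern 0, 0.5, 0.5, 0 is unchanged if first and last are swapped, so in half of the significant results the final mean lies above baseline by chance: 54% / 2 = 27%, still far above 2.5%.

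**A real gain (k = 4, n = 26).**

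| Pattern | Gain | F | Contrast |
|---|---|---|---|
| Steady rise | 0.5 SD | 31% | 43% |
| Step at wave 2, held | 0.5 SD | 42% | 43% |
| Step at wave 3, held | 0.5 SD | 54% | 43% |
| Steady rise | 0.8 SD | 71% | 82% |
| Step at wave 2, held | 0.8 SD | 84% | 82% |
| Step at wave 3, held | 0.8 SD | 93% | 82% |

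For the 0.5 SD steady rise, λ = 26 × 0.1389 = 3.61 and δ = 0.5 / √(2/26) = 1.80. F therefore loses power for gradual change only.

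**Limiting case.** With two waves F = t², so the two tests coincide and the intermediate-wave problem disappears.

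**The case against.** A condensed article may name the model family and leave the contrast to a fuller plan, and the Analysis plan does mention follow-up analyses. That has some weight. But the mention sits in the paragraph on count and regression models and names no comparison, and the article itself states the hypothesis, the test and the support rule, which do not fit together. If the contrast were run only after a significant F, the false-gain rate would return to about 2.5%, but for a steady 0.8 SD rise power would be 0.68 against 0.82 for the contrast alone (simulation, four waves, 104 in total).

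A reader might infer that a fall in scores could be declared support, since F has no direction. The documents do not support pressing this. The hypothesis itself says higher, so a significant fall would not satisfy it, and the nurses' paired t-test is equally silent on direction. A reader might also infer that the ANOVA generally costs power. It does not: with phased training a stepped gain is plausible, and there F does about as well or better.

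The number of people-survey waves is not shown. The four quarterly points are stated for the evaluation as a whole. Choosing an ANOVA, in explicit contrast to a t-test, suggests more than two waves but does not prove it. Finally, an over-time test does serve the article's interest in short- and medium-term outcomes, which is a reason to keep it as a secondary result.

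**Conclusion.** The mismatch holds. For the people measures, the named test answers whether scores differ anywhere over time, while the hypothesis asks whether the final wave is above baseline. That needs no assumed effect size, only more than two survey waves, which is likely but not confirmed.

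The size does rest on assumptions. At 0.5 SD with 104 analysable responses, a temporary intermediate change with no net gain makes F significant in roughly 32% to 55% of trials over the patterns and wave counts examined, against 2.5% for the contrast. The effect sizes are illustrative, since the article gives none.

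This is a should-fix point with moderate confidence. It concerns two of four measures in an uncontrolled within-group comparison, and leaves the first objective (restrictive practices and injuries) untouched.

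**What to change.** In the Analysis plan, name one planned contrast, final minus baseline, from the same ANOVA model (all waves kept for the pooled variance) as the test of the hypothesis for CEO-MHS and VPC-M-FR. Test it two-sided at 5% and declare support only if the difference is positive. If distributional assumptions fail, use a two-sample rank test of final against baseline.

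Keep the F test and the intermediate-wave comparisons as secondary results for the short- and medium-term outcomes described under Design. In the Sample size section, say whether the 95% power refers to this contrast or to the F test, and state how many waves the people survey has.

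The cost is a few sentences of wording and no new data. Intermediate-wave differences no longer count towards support for this hypothesis, and if the true pattern is a late sustained step the contrast is somewhat less powerful than F.

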### Sample size

The sample size for this evaluation was determined using a combination of power analyses, prior research findings, and feasibility considerations. Both quantitative and qualitative approaches were employed.

For event-based analyses, Monte Carlo simulations using the simr package [59] and RStudio [60], were used to estimate the necessary duration of data collection. A Poisson mixed-effects model was applied to synthetic data replicating the initial implementation outcome parameters. To detect a 12% reduction in seclusion rates with 99.30% power, at least 3.60 months of data collection is required. To identify significant changes in physical restraint incidents, a 12-month period is necessary to achieve 90.60% power. In comparison, 10.8 months are required to detect differences in Code Black/ Assist events with 85.20% power. These calculations include a 20% buffer to account for potential attrition and were conducted with an alpha level of 0.50, aligning effect size assumptions with findings from the NSW Safewards evaluation [61]. The NSW Safewards evaluation was chosen as a reference, due to its high methodological quality and relevance to the same geographic and service context as this evaluation, being the only study identified in an overview of systematic reviews with such characteristics [5].

For survey-based measures, sample size estimations were conducted using G*Power 3 [62]. Based on power calculations, a minimum of 135 individual survey responses is required across intervention sites, incorporating a 30% margin for potential exclusions to achieve 95% power. Similarly, a minimum of 60 nurse surveys is necessary, maintaining the same power assumptions and buffer levels.

For the qualitative component, data will be collected through semi-structured interviews and focus groups. At least 15 individual interviews will be conducted at T2 and T4, with additional interviews, if necessary, until data saturation is reached. Additionally, three to five focus group discussions will be conducted per site, including six nurses involved in intervention implementation since baseline. These sample size decisions are informed by systematic reviews on qualitative research methodologies, indicating that such numbers are typically sufficient to achieve thematic saturation in studies using interviews [63] or focus groups [64].

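### The people-survey hypothesis compares the final time point with baseline, but the planned omnibus ANOVA does not test that contrast and can be significant from mid-study differences alone

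*Protocol article*

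**What the plan says.** The introduction (section The Safe Steps for De-escalation) states the second hypothesis as "scores from these four measures at the final time point would be significantly higher than at baseline". Two of the four measures come from people receiving care: service experience and perceived staff action on violence prevention. The Design section repeats the hypothesis, again that scores "at the final time point would be significantly higher than at baseline".

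The Analysis plan sets the test for these measures: "a one-way analysis of variance will be used to assess differences over time in people measures". For the nurse survey it chooses differently: "a paired t-test will examine changes in nurses’ measures over time". The support rule, given once for all hypotheses, is "Each hypothesis will be supported if outcomes are statistically significant at p < .05".

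On timing, the Design section says "Four quarterly time points will be applied" and ties these points to short-, medium- and long-term outcomes. Under Sample size, "a minimum of 135 individual survey responses is required across intervention sites, incorporating a 30% margin for potential exclusions to achieve 95% power".

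**The concern.** The hypothesis is a single comparison of two named time points, with a stated direction. A one-way ANOVA over time tests whether any of the wave means differ. With only two waves, the two questions coincide apart from direction. With three or more they do not: F can be significant because of what happened between baseline and the final wave, while those two are equal.

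The support rule attaches to statistical significance and names no contrast. Applied as written, it leaves open after the data are seen which comparison between time points carries the hypothesis. At stake is a published statement that service experience or perceived staff action improved, resting on a test that did not examine final against baseline.

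**Working it through.** **The plan's own figure.** The 135 responses cannot be reproduced, because the article gives no effect size, number of groups or test for it. At 95% power, alpha .05 and four groups, Cohen's f = 0.25 needs 280 before any margin. With f = 0.40 it needs 112, which becomes 146 (×1.3) or 160 (÷0.7). Three groups with f = 0.40 gives 102 × 1.3 = 133, which is close, but those inputs are guesses. Nothing below depends on this figure except the number of usable responses.

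**Inputs.**
- Usable responses: 135/1.3 ≈ 104. Range: 135 × 0.7 ≈ 94 up to 135 if nobody is excluded.
- Waves: k = 4, equal in size (assumed, from the four quarterly points). k = 5 is tried as well, in case baseline is an extra wave.
- Independent responses, SD = 1, alpha .05 (the independence and equal SD are assumed).

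**Formulas.** With n responses per wave, the omnibus F has k − 1 and k(n − 1) degrees of freedom and non-centrality λ = n Σ(μ − mean)². The final-minus-baseline contrast is a t test on k(n − 1) degrees of freedom with non-centrality δ/√(2/n).

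**Mid-study difference only.** Means (0, −0.5, −0.5, 0), so final equals baseline. The grand mean is −0.25 and every deviation is 0.25 in size, so Σ = 4 × 0.0625 = 0.25.

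| Responses used | k | n per wave | λ | P(F significant) |
|---|---|---|---|---|
| 104 | 4 | 26 | 26 × 0.25 = 6.50 | 54% |
| 92 (of 94) | 4 | 23 | 23 × 0.25 = 5.75 | 48% |
| 132 (of 135) | 4 | 33 | 33 × 0.25 = 8.25 | 65% |
| 105 | 5 | 21 | 21 × 0.30 = 6.30 | 47% |

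The last row uses (0, −0.5, −0.5, −0.5, 0): the mean is −0.3 and Σ = 2 × 0.09 + 3 × 0.04 = 0.30. In every row, a final-minus-baseline contrast whose 95% interval must lie above zero gives false support 2.5% of the time.

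**Power when the final score is truly +0.8 SD** (k = 4, n = 26). The contrast has non-centrality 0.8/√(2/26) = 2.88 and power 81.5%, whatever the middle waves do. The omnibus F depends on them:

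| Wave means | Σ | λ | Omnibus | Contrast |
|---|---|---|---|---|
| 0, 0.27, 0.53, 0.8 | 0.356 | 9.24 | 70.5% | 81.5% |
| 0, 0.4, 0.8, 0.8 | 0.440 | 11.44 | 80.4% | 81.5% |
| 0, 0.8, 0.8, 0.8 | 0.480 | 12.48 | 84.0% | 81.5% |
| 0, 0, 0.8, 0.8 | 0.640 | 16.64 | 93.4% | 81.5% |

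The contrast gains for a steady rise, roughly ties in the second pattern, and loses for the last two.

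**The case against.** Several points on the other side have weight.

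- **Direction.** A reader might infer that the rule would declare improvement if scores fell. F does ignore direction: a steady fall to −0.8 SD is significant as often as the matching rise, 70.5%. But the rule refers back to a hypothesis that says higher, so a plain fall would hardly be reported as support. What stands is that direction must be inferred and is not part of the rule.
- **Follow-up comparisons.** An omnibus ANOVA is usually followed by contrasts, and the Analysis plan does say "Data cleaning and validation, assumption checks, model diagnostics, and follow-up analyses will be undertaken". An analysis plan that is not shown may name them. However, that sentence belongs to the paragraph on count and regression models, names no contrast, and is not part of the support rule. The article itself fixes the hypothesis, the test and the rule, and these three do not match.
- **Number of waves.** The people-survey schedule is in a figure that is not shown. With two waves the mid-study problem disappears. Four quarterly points, and the choice of ANOVA where the nurses get a paired t-test, make more than two waves likely but not certain.
- **Power.** A reader might infer that the omnibus test wastes power. The second table does not support that as a general claim.
- **Intermediate waves.** They serve the stated short- and medium-term aims, so comparing them has a purpose. This is accepted in the fix.
- **Unit mix.** A reader might infer that shifts in the mix of units are already known to distort the result. The document gives no figure for this, and it does not say that respondents differ from wave to wave. Approaching people before discharge makes that probable, no more.

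**Conclusion.** The point holds in a limited form. The planned test of the people measures is not a test of the stated hypothesis, and with three or more waves a significant result can arise entirely from mid-study differences. The illustrative size is about 54% for a 0.5 SD dip at both middle waves, and 47% to 65% over the sample sizes and wave numbers tried, against 2.5% for the planned contrast. These percentages rest on an assumed pattern, equal waves, independent responses and a wave count that cannot be confirmed from the text. The mismatch itself needs only three or more waves. No general power loss is shown. These measures belong to the second objective, so the restrictive-practice and injury results are unaffected.

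**What to change.** State that, for each people measure, the hypothesis is decided by one pre-specified contrast, final minus baseline, from a linear model with time point as a factor. It is supported only if the 95% interval lies above zero. That puts both the comparison and its direction into the rule.

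Add unit as a factor. The Setting section says the three intervention units differ in care models and restrictive practice rates, the event models already carry unit as a covariate, and respondents are probably mostly different people at each wave.

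Keep the across-wave comparison as a secondary analysis for the short- and medium-term aims, and say that it does not decide the hypothesis.

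The cost is a sentence or two of text and two degrees of freedom for three units. No further data are needed. Depending on the trajectory, power for the hypothesis may be somewhat higher or lower than with the omnibus F.
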